**Figure 1 F1:**
[figure not shown]
Study design of the POLEM trial. *Capecitabine chemotherapy for 24 weeks or capecitabine/oxaliplatin for 12 weeks. dMMR, deficient mismatch repair; MSI-H, microsatellite instability high; MSS, microsatellite stable; pMMR, proficient mismatch repair.

### Study objectives and endpoints

#### Primary endpoint

The primary endpoint is DFS at 3 years. This is defined as the proportion of subjects who are alive and disease free at 3 years. For subjects who neither progressed nor died, their DFS time will be censored at the last date of contact. The main analysis will take place once 60 events have occurred.

Relapse will be based on investigator reported imaging assessments or colonoscopy. Where a patient has neither progressed nor died, their DFS time will be censored at the last date of contact (known to be alive and relapse free).

#### Secondary endpoints

Median DFS will be reported with a 95% CIs in each group.OS at 5 and 7 years is defined as the proportion of patients who are alive at 5 and 7 years, respectively. Patients alive at the time of analysis will be censored at the date of last follow-up. Analysis methods for OS will follow those of the primary endpoint DFS (see primary endpoints above).Median OS will also be reported as DFS section above.Adverse events as assessed by National Cancer Institute Common Terminology Criteria for Adverse Events V.4.0Health-related quality of life based on EORTC QLQ C-30 and 5-level EuroQol 5 Dimensions: QLQ C-30 will be summarised over time, as per the standard scoring manual, for each of the 15 domains using mean and SD. Statistical analysis will consist of linear mixed models and the mean difference between treatments for each domain score will be presented.Quality-adjusted life years (QALYs).Health resource use: health resource use will be collected prospectively postrandomisation a healthcare services resource questionnaire designed for the trial.

Resource use and associated costs will be combined with quality-of-life data to provide a cost per QALY for fluoropyrimidine-based adjuvant chemotherapy, followed by avelumab compared with standard fluoropyrimidine-based adjuvant chemotherapy alone. In terms of analysis, Kaplan-Meier plots will be used to summarise the survival estimates and report the DFS rate at 3 years along with a 95% CIs in each group. DFS rates between groups will be compared using the log-rank test. In addition, Cox proportional hazards (PH) model (or alternative methods, eg, method of Klein) will be used to compare the DFS rates overall and at 3 years adjusting for prespecified covariates. A test for non-PH will also be carried out.

The primary analysis for DFS outcome will be unadjusted and will be based on the intention-to-treat (ITT) population with a sensitivity analysis in the modified ITT population and in the per-protocol population.

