
ALT, alanine transaminase; AST, aspartate transaminase; ECOG PS, Eastern Cooperative Oncology Group performance status; NCI-CTCAE, National Cancer Institute Common Terminology Criteria for Adverse Events.

According to the statistical design, 402 patients (201 per arm) are to be randomised. It is expected that approximately 4000 participants will need to be screened in order to recruit 402 patients to the study, assuming an incidence of dMMR/MSI-H of 10%–15% and an incidence of *POLE* mutations of 8%–10% in patients under 50 years of age.^21^ Considering the time required to obtain local approval and to initiate all participating centres, the study is expected to take up to 36 months to complete accrual.

There are no proscriptive criteria for surgical resection of the primary tumour in this trial. However, it is expected that resection of the tumour will be undertaken in the elective setting by a colorectal specialist surgeon.

Tumour MMR/MSI status will be routinely tested locally as per NICE guidelines^17^ either in the preoperative biopsy or resection specimen. Patients whose tumours are dMMR/MSI-H can provide consent to the main study and undergo the study screening procedures. If they are found to fulfil all eligibility criteria, then they will be randomised. Patients who are aged below 50 years and whose tumours are pMMR/MSS, will be asked to sign a pre-screening consent for the centralised analysis of *POLE* exonuclease domain mutations. Those who have tumours harbouring these mutations can sign the main study consent and undergo the study screening procedures. If they are found to fulfil all eligibility criteria, then they will be randomised.

All eligible patients who are randomised will receive standard fluoropyrimidine-based adjuvant chemotherapy for 12 or 24 weeks depending on the decision of the local investigator. The choice of adjuvant chemotherapy (ie, 24 weeks of single agent fluoropyrimidine chemotherapy or 12 weeks of doublet, oxaliplatin-based chemotherapy) must be declared by the investigator at study entry before randomisation. The adjuvant chemotherapy regimen and MMR/MSI status will be used as stratification factors.

At the end of adjuvant chemotherapy, patients who are randomised to the investigational arm will receive additional 24 weeks of treatment with avelumab (figure 1).

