### Sample size calculation

The 3-year DFS rate in the control arm is expected to be about 75%.^24^ The experimental treatment (fluoropyrimidine-based chemotherapy followed by avelumab) is expected to improve the 3-year DFS rate by 12% (to 87%), corresponding to an HR of 0.48. This effect size is justifiable since the population is highly enriched (with dMMR/MSI-H and *POLE* mutant patients) and second, a large effect size will also allow potential for cost-effectiveness of the experimental intervention.

Therefore, a sample size of at least 171 per group (342 in total) is required (60 DFS events in total) to reject the null hypothesis of:

H_0_; HR=1 vs H_1_: HR HR≠1 with at least 80% power assuming a two-sided 5% type I error.

Assuming further a 15% drop-out rate (lost to follow-up rate) a total sample size of 402 will be required (201 per group in a 1:1 randomisation).

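### The primary DFS test ignores the factors used to stratify randomisation: it is valid, but mildly conservative if those factors are strongly prognostic

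*Protocol article*

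**What the plan says.** In the protocol article, under Study design and treatment, the investigator must declare the chemotherapy regimen before randomisation, and "The adjuvant chemotherapy regimen and MMR/MSI status will be used as stratification factors".

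The analysis paragraphs stand under Secondary endpoints. They compare DFS by a log-rank test and settle the primary analysis: "The primary analysis for DFS outcome will be unadjusted and will be based on the intention-to-treat (ITT) population". A Cox model, or an alternative method, is planned as an addition. It adjusts for covariates that the article says are prespecified but does not name. OS is to be analysed by the same methods as DFS.

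Under Sample size calculation the design is sized "with at least 80% power assuming a two-sided 5% type I error". Under Primary endpoint the timing is fixed: "The main analysis will take place once 60 events have occurred".

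**The concern.** Stratified randomisation balances the arms within each stratum, which removes part of the chance variation between them. An unstratified log-rank test computes its variance as if that variation were still present. If the factors are prognostic, the variance is somewhat too large, so the test rejects a little less often than it should, both under the null hypothesis and under the alternative.

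Being unadjusted is a stated choice here, not a detail left to the SAP. The additional Cox model does not change which test decides the trial. With 60 events and a power target met almost exactly, even a small loss of efficiency is worth avoiding if that costs next to nothing.

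**Working it through.** **Inputs from the document.** Control arm: "The 3-year DFS rate in the control arm is expected to be about 75"%. Effect: "improve the 3-year DFS rate by 12% (to 87%), corresponding to an HR of 0.48". Size: "a sample size of at least 171 per group (342 in total) is required (60 DFS events in total". Loss: "Assuming further a 15% drop-out rate (lost to follow-up rate) a total sample size of 402 will be required". Accrual takes up to 36 months and allocation is 1:1.

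**Step 1. Reproduce the plan's figures.**
- HR = ln 0.87 / ln 0.75 = 0.484.
- Schoenfeld events = 4(1.960 + 0.842)² / (ln 0.484)² = 31.4 / 0.526 = 59.6, so 60. With HR rounded to 0.48 it is 59.
- Power at 60 events and HR 0.484 = Φ(√60/2 × 0.7255 − 1.960) = Φ(0.85) = 80.2%.
- Inflation for loss: 342 / 0.85 = 402.4, against the stated 402.

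The stated events and total are reproduced. The calculation is for an unadjusted comparison, so it agrees with the stated primary analysis. The Schoenfeld event count is the same for a stratified log-rank test.

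**Step 2. Compare the two tests by simulation.** Common settings: 402 patients, permuted blocks of 4 within strata, 15% loss by 3 years, pooled control 3-year DFS of 75%, cut at the 60th event, HR about 0.48 within strata. Stratum sizes and prognostic ratios are assumptions, because the document gives neither.

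*Both factors, 20,000 runs per scenario (simulation SE about 0.3 points for power, 0.15 for type I error). The minority MMR/POLE stratum is 10%. The poorer-prognosis regimen stratum is 30% in the first two rows and 50% in the last two.*

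| Prognostic HR: regimen, MMR | Power, unstratified vs stratified | Type I error, unstratified vs stratified |
|---|---|---|
| 1, 1 | 79.3% vs 79.1% | 5.1% vs 5.2% |
| 1.5, 1.5 | 79.5% vs 79.3% | 4.9% vs 5.0% |
| 2, 2 | 78.6% vs 79.4% | 4.7% vs 4.9% |
| 3, 2 | 78.1% vs 79.4% | 4.5% vs 5.0% |

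*Regimen effect only, 50/50 split, 8,000 runs for power (SE about 0.5 points) and 12,000 for type I error (SE about 0.2).*

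| Regimen HR | Power, unstratified vs stratified | Type I error, unstratified vs stratified |
|---|---|---|
| 1 | 78.5% vs 78.3% | 5.2% vs 5.2% |
| 2 | 78.1% vs 78.4% | not reported |
| 3 | 78.0% vs 79.4% | 4.5% vs 5.1% |
| 4 | 77.2% vs 79.4% | 4.4% vs 4.7% |

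Power is a little under 80% even with no prognostic effect. That shortfall from Schoenfeld's approximation is common to both tests and does not bear on the comparison.

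**Step 3. Check the effect definition.** A within-stratum HR of 0.484 at ratio 4 gives a pooled experimental 3-year DFS of 86.6%, slightly below the planned 87%. With the pooled rates held at 75% and 87% instead (6,000 runs), unstratified power is 78.4%, 78.9%, 79.5% and 79.2% at ratios 1, 2, 3 and 4. Against its own design target the unadjusted test therefore loses nothing. The stratified test still gains about 1 to 2 points at the higher ratios and is 0.4 points lower at ratio 1, which is within simulation error.

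**The case against.** The strongest reply is that nothing here is wrong. A prespecified unadjusted ITT log-rank test is valid, its type I error is not inflated, and it matches the basis of the sample size. Any miscalibration is towards caution. The primary endpoint is defined as a proportion disease-free at 3 years, which is a marginal quantity and suits an unadjusted comparison. An adjusted Cox model is already planned, and its covariates may well be named in the SAP. With 60 events and a possibly small POLE stratum, leaving strata out also avoids a contingency rule. All of this stands. It limits the size of the point but does not remove the mismatch between randomisation and primary test.

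Three stronger readings are tempting, and the document supports none of them.
- A reader might infer that power and calibration are being thrown away. That depends on prognostic strength, which is not given. The document says only that the local investigator chooses the regimen, not that the choice follows prognosis. Step 3 also shows no loss against the plan's own target.
- A reader might infer that the unadjusted HR is biased towards 1. The shift is the difference between a marginal and a conditional HR, and it is tiny: 0.485 unstratified against 0.477 stratified at ratio 3.
- A reader might infer that stratifying would deal with avelumab starting after 12 or 24 weeks of chemotherapy. It would not. Stratification gives each regimen its own baseline hazard but still assumes one constant treatment effect. The article plans a separate test for non-proportional hazards.

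**Conclusion.** The point holds as a small improvement, not as an error. The primary test leaves out the factors that structured the randomisation. It remains valid and consistent with the sample size, with mild conservatism only if those factors are strongly prognostic: about 4.5% type I error and about 1 to 2 points of power at assumed ratios of 3 to 4, under about 1 point at ratios of about 2 or less, and nothing measurable if they are not prognostic.

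The direction is secure, since the separate sets of simulations agree on it. The size rests on assumed stratum fractions (30% to 50% in the poorer-prognosis regimen stratum, about 10% or less in the minority MMR/POLE stratum) and assumed prognostic ratios.

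**What to change.** - Make the primary test a log-rank test stratified by the regimen declared at randomisation and by MMR/MSI status, and take the HR from a Cox model stratified the same way. Because OS follows the DFS methods, say whether the change applies there too.
- Prespecify a rule, applied blind to treatment, for pooling over MMR/MSI status if the pMMR/POLE stratum has too few events.
- Keep the unadjusted log-rank test and the Kaplan-Meier 3-year rates as the sensitivity or marginal analysis.
- If the sponsor prefers to keep the unadjusted test as primary, at least name both stratification factors among the covariates of the adjusted Cox model.

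The cost is a few sentences of protocol or SAP wording, with no new patients, events or data and no change to the 60-event target. The small downsides are the extra pooling rule and a headline HR that is conditional on stratum instead of marginal.

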### Sample size calculation

The 3-year DFS rate in the control arm is expected to be about 75%.^24^ The experimental treatment (fluoropyrimidine-based chemotherapy followed by avelumab) is expected to improve the 3-year DFS rate by 12% (to 87%), corresponding to an HR of 0.48. This effect size is justifiable since the population is highly enriched (with dMMR/MSI-H and *POLE* mutant patients) and second, a large effect size will also allow potential for cost-effectiveness of the experimental intervention.

Therefore, a sample size of at least 171 per group (342 in total) is required (60 DFS events in total) to reject the null hypothesis of:

H_0_; HR=1 vs H_1_: HR HR≠1 with at least 80% power assuming a two-sided 5% type I error.

Assuming further a 15% drop-out rate (lost to follow-up rate) a total sample size of 402 will be required (201 per group in a 1:1 randomisation).

### Planned recruitment

The incidence of stage III dMMR/MSI-H CRC is reported to be about 1753 per year in the UK (England and Scotland) (based on 41 112 CRC patients diagnosed in UK in 2013 (latest figures), 23.7% of these are stage III and 18% of them are dMMR/MSI-H). Assume some 20% of these may fail screening/eligibility criteria, the pool of patients available for recruitment is likely to be approximately 1500 per year.

With a target of 402 patients, assuming recruitment over 36 months, on average, about 11 patients per month are anticipated (ie, 400/36=~11/ month). At least 30 sites are planned to be activated. Hence, on average, <1 patient per month is required per site. Assuming that recruitment will not be heavily competitive as the number of CRC trials in this setting are few, the target sample size is expected to be reached.

## Discussion

The POLEM trial is one of two studies evaluating checkpoint inhibitor drugs in the adjuvant setting in stage III dMMR/MSI-H colon cancer; the other being the US-based ATOMIC study (ClinicalTrials.gov Identifier: NCT02912559). POLEM is distinct from ATOMIC in that it also includes *POLE* mutant colon cancers and has been designed to incorporate the recent IDEA collaboration trial data comparing 3 months vs 6 months fluoropyrimidine-based chemotherapy.^25^ The study opened in August 2018 and will be conducted in over at least 30 UK sites with potential for international collaboration. We anticipate that the findings could change the standard of care in this molecularly defined stage III colon cancer population.
